### Process evaluation

In line with MRC guidelines [43, 44] an embedded mixed methods process evaluation will be implemented to assess intervention fidelity and provide a contextualised analysis of intervention delivery.

During the first stage of the study, the process evaluation focused on the feasibility and acceptability of the study procedures. Quantitative programme activity data was collected to assess adherence to fidelity and recruitment targets, while qualitative interviews with participants (*n* = 8) and staff (*n* = 12) were conducted to investigate the acceptability of study procedures and the recruitment and randomisation processes. We gave particular attention to attitudes towards randomisation to the waiting list control group.

During the main trial**,** the process evaluation will seek to describe the implementation of the intervention, continue to assess intervention fidelity and implement a multi-perspective qualitative investigation of intervention delivery. Routine data is collected on programme recruitment, registration, referrals, attendance, retention and staffing. Data is also collected on participation, reach, dose received (number of sessions attended), and retention rate (overall rates and in particular with reference to socio-economic position and ethnic diversity of sample). Fidelity measures are completed by staff delivering the programme at the end of each session. Additionally, an adapted version of the Parent Programme Implementation Checklist [45] will be used to assess fidelity during observation visits carried out by the research team in a random sample of programmes.

During the main trial, qualitative data collection will be extended to include individual semi-structured interviews with lead commissioners (*n* = 7) and SFSC programme coordinators (*n* = 7) across each area. In addition, we will complete individual semi-structured interviews with staff and participants, including staff involved in delivering the programme across the seven areas (*n* = 21) and participants (*n* = 20). The participants will be a purposive sample selected to represent range and diversity in terms of age of index child, ethnicity and other demographic characteristics.

#### Analysis of process evaluation data

Quantitative data on fidelity and engagement (attendance and retention) and service activity will be subject to descriptive analyses. Qualitative interviews will be audio recorded, professionally verbatim transcribed and translated where necessary before being subjected to a thematic analysis [46]. This will be supported by use of Nvivo and involve initial data organisation through coding, category development and then testing. Analysis will focus in particular on exploring the range of views on the relevance, appropriateness and acceptability of the programme, perceived barriers and facilitators to change in parenting approaches, how the programme helped or hindered this in the family environment, and examine whether, and how, intervention delivery and outcome generation are influenced, either positively or negatively, by contextual factors. In this way the process evaluation will generate empirical data which will enable mechanisms of action to be described and the underlying theory of change to be evaluated. The work will be undertaken in parallel with the trial and will support interpretation of trial outcome data, thereby increasing the explanatory potential of the study while also potentially informing strategies for downstream implementation of the intervention.

### Patient and public involvement (PPI)

Public involvement is essential in all stages of public health research. It is particularly important in the evaluation of complex interventions that seek to support and empower families living in challenging circumstances, and from marginalised communities to further develop their parenting skills and abilities. The study includes four main strands to PPI:

### Ethics

Ethical approval for the study was given by the UCL Research Ethics Committee (reference 1538/002) on the 27th of February 2019.

### Trial supervision and oversight

Two independent oversight committees (Trial Steering Committee and Data Monitoring and Ethics Committee) have been established to oversee the supervision and governance of the trial. In addition, a Trial Management Group oversees the on-going implementation and conduct of the study. These committees and group function in accordance with the NWORTH, Bangor CTU standard operating procedures.

#### Initial implementation of the trial: insights and challenges

In the next section, we report on the implementation of the trial in the internal pilot and the challenges and adaptations to the original protocol that have occurred to date.

#### Progression to full trial

RAG (red/amber/green) progression criteria [47] were used to assess the randomisation, retention and intervention attendance to determine whether the stage 2 main trial could proceed (see Table 1). In line with the RAG criteria outline, ACCEPT criteria were used to determine whether pilot data could be included in the main trial [48].

**Table 1 Tab1:** RAG progression criteria

Indicator	Green	Amber	Red
Randomisation: 130 participants, either: (a) across all 5 sites/programmes OR (b) if one or two sites significantly underperforms, across the best four or three sites	More than 80%	40–80%	Less than 40%
Retention: at 3-months post intervention (around 6-months from baseline)	More than 85%	50–85%	Less than 50%
Attendance: proportion attending at least nine out of the 13 programme sessions	More than 70%	50–70%	Less than 50%
Completeness of data: on an outcome measure at baseline and post-intervention	Less than 20% missing data		
Intervention fidelity	Completion of facilitator self-assessment and quality assessment		

Based on the progression RAG criteria, progression to full trial was warranted. The total number of randomisations across the five internal pilot sites for the first 6 months of recruitment was 123, which is 95% of the target for this period and achieves a progression criterion of green. Only 14 participants withdrew from the internal pilot study prior to the 3 months follow-up. Therefore, the retention rate for the 3 months follow-up was 89% (109/123), which achieves a progression criterion of green. The median number of sessions of the SFSC programme attended by participants was 9 out of 13. The percentage of participants attending nine or more sessions was 51%, which achieves a progression criterion of amber.

Data completion - For both timepoints, and for all outcome measures the percentage of missing data was substantially less than 20%. Hence, all outcome measures are deemed acceptable for the full-scale trial.

Intervention fidelity - Overall, the feedback from facilitators on the SFSC programme regarding the quality and fidelity of the intervention was positive. Participants were motivated and engaged. Participants bonded well with other group members and were willing to share their real-life experiences with the group. Notably, the sessions with the community speaker were typically well received. However, for some sessions there were issues with low attendance, sessions over-running and participants being distracted.

#### Interviews with participants and delivery staff

This section draws on analysis from qualitative interviews with eight parents who took part in the internal pilot and 12 members of staff involved in commissioning or delivering SFSC during the pilot phase.

Parents appeared to accept and understand the randomisation process although the reasons for the study design were not always fully understood. Parents were generally accepting of the waitlist design. This view was echoed by the research team who found that most parents they recruited accepted the chance they may be allocated to the waitlist. Services on the other hand expressed some reservations about the randomisation process. Services were sometimes found to “gatekeep” participants by deciding which parents to invite for the study based on their assessment of need. Ongoing communications between the research team and members of staff was vital and the research team learned that it is of upmost importance that services understand, and are committed to being part of the research (and the randomisation process) before taking part. For engagement with new sites the research team will ensure that services only take part when fully comfortable with the randomisation process. To increase the understanding and acceptance of the randomisation process, as well as to maintain enthusiasm and engagement with the research, the research team has introduced quarterly study newsletters and delivered webinars. During these webinars, we discuss the research and encourage services to learn from each other’s experiences and hear from PPI members about their views on the research processes.

Staff interviews and reflections from the research team also revealed that it is vital that those delivering the programme are fully aware of their role in the research. Facilitators stated that their managers had not always informed them of their part in the research study from the start, creating some resistance. The research team will ensure that in communications with commissioners, service managers and decision makers it is stressed that facilitators should be involved early on in discussions and made aware of their part in the research. Similarly, some facilitators work on a freelance basis and although refresher training and research trainings are offered for free, facilitators were slightly reluctant to offer their time to engage with training without being compensated. The research team will use the excess treatment costs to compensate freelance facilitators for their part in the main trial.

#### Reflections from research team

As is common in most trials, recruitment of parents into the trial was challenging at times. Although services are asked to recruit twice as many parents into their programme as usual, initial discussions with Local Authorities and community organisations delivering SFSC suggested they felt confident in recruiting the required numbers within a relatively short period (4 weeks). The research team’s experience to date is that services overestimate the number of parents on their waitlist and that a wider and more structured outreach plan to recruit parents is necessary. We have worked hard to improve the recruitment strategy during the early stages of the trial. The interviews with parents and feedback from PPI members suggest that we should aim to appeal to people’s altruism when asking them to be a part of the study. We have therefore updated the recruitment materials accordingly. We have widened the recruitment window and ask services to start outreach earlier than they normally would. We now promote different approaches within services such as recruitment events, the use of local schools, social media, online events and engagement with referrers.

#### Impact of the COVID-19 pandemic

The emergence of the COVID-19 pandemic created challenges for the trial. In line with government social distancing and lockdown guidelines, all face-to face-delivery of the SFSC programme was paused between March 2020 and September 2020. Face-to-face delivery and recruitment into the trial resumed in November 2020 but the intervention delivery, method of recruitment and data collection have been modified to minimise transmission of the virus and protect participants, research staff and service delivery staff. Ethics approval was granted to make the following changes which are included in the latest protocol version 4 (16th February, 2021):
Intervention delivery – SFSC programmes that are running face to face can offer online group support to those participants who are not able to attend due to COVID-19 restrictions.Recruitment – baseline interviews are conducted via video or telephone calls. Consent is obtained remotely by asking participants to return a digital copy of the consent form and, if this is not possible, through audio recording the consent process by reading through the consent form with the participant, and asking them to respond to each point. These recordings are subsequently stored securely in encrypted files.Data collection – all data are collected remotely via video call or telephone call when video call is not possible. Ethical approval was gained for the change in recruitment and data collection methods.Sample size - Due to the impact of COVID-19 social distancing restrictions, the sample size has been reviewed and revised to 672 participants (360 intervention: 312 control). The changes undertaken still accommodate the power to assess the effects originally planned. The sample initially allowed for clustering within both arms, despite there being none in the control arm, the inflation in the control arm was kept to accommodate an anticipated differential drop out. This differential drop out was not evident in the internal pilot and therefore this inflation has been removed. The recalculation also allows for variation in the size of the recruited groups from 6 to 13 to accommodate the varying group sizes due to social distancing restrictions on venues. Recalculation of the sample therefore results in an unequal allocation ratio with the optimal allocation ratio of 1.154 to 1 being employed.

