### Randomisation

Randomisation is via a secure online system using a sequentially randomised dynamic adaptive algorithm [24], stratified by site, gender of parent, and self-referral status, with a 1:1 allocation ratio. Participants are randomised by a member of the research team after consent and baseline questionnaires have been completed. To maintain blinding, the researcher randomising the participant will not be involved in collecting follow-up data. All researchers involved in follow-up data collection will be asked to complete a questionnaire to determine their perception of group allocation for each participant.

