### Sample size calculation

We calculated that a sample of 676 participants was needed to detect an effect size of 0.3 with 90% power at a 5% significance level and assuming an intraclass correlation coefficient (ICC) of 0.05 [35], including 20% attrition rate. This assumed 26 clusters of 13 participants per cluster within the intervention arm (*n* = 338) and 338 participants recruited to the waiting list control arm (1:1 allocation ratio). An effect size of 0.3 on the WEMWBS is indicative of a change of 3 points on the scale stated as clinically relevant by the scale manual [36] and assuming a standard deviation of 10 as seen in a similar population [37]. For the total SDQ score, the key secondary outcome, a minimal clinically significant change is 2 as indicated by Ford and colleagues [38]. Taking a SD of 6 from normative data held by ‘*youthinmind’* [39], then an effect size of 0.33 is indicated. If the ICC is assumed equivalent to that of the parental outcome, then a sample of 676 indicates 87% power; with a reduced ICC of 0.025, this power increases to 92%.

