### Statistical and economic analysis

Analysis will be conducted on an intention to treat basis. The main analysis will be mixed effects models adjusted for baseline score, allocation group, and stratification variables. Site will be included as a random effect. To minimise bias due to missing data, predictors of missingness will be investigated using regression models and any predictors found will be considered for inclusion in the models. Multiple imputation will be employed to address missing scores where appropriate. Analysis of complete case data will be carried out as a sensitivity analysis to establish the sensitivity of the treatment effect estimates to the missing data. All treatment effect estimates will be presented with 95% confidence intervals. Additional regression analyses will explore factors associated with effectiveness. Exploratory analysis will initially look at including a measure of adherence within the models to assess the levels of effectiveness. Depending on the exact socio-demographic nature and diversity of the sample once the recruitment stage is completed, exploratory sub-group analysis will investigate different aspects of inequalities in the effectiveness of the intervention across the study population. Information with regard to data entry, coding, security, and storage is documented in a data management plan, which is available on request.

An economic evaluation will be conducted, following the recommendations of the NICE Public Health Reference Case [40]. The analysis will take a public sector perspective, estimating cost and cost effectiveness for the within-trial period. Cost effectiveness will be evaluated using a cost-utility analysis (CUA) and cost-consequences analysis (CCA). We will undertake a detailed cost analysis to estimate the costs of delivering the SFSC programme, including: development and training of accredited providers; the cost of delivering the group sessions; participant monitoring activities; and any follow-up/management. Broader resource utilisation over and above the costs of the SFSC programme will be captured via parent questionnaires administered at each data collection time point. Resource use data will be collected on NHS, social care, criminal justice system, and education contacts. Unit costs will be derived from local and national sources and estimated in line with best practice. Costs will be standardised to constant prices.

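### The allocation ratio changed from 1:1 to 1.154:1 during the trial, but the stated main model has no term for randomisation period

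*Protocol article*

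**What the plan says.** The Randomisation section describes a dynamic adaptive algorithm, "stratified by site, gender of parent, and self-referral status, with a 1:1 allocation ratio". The Sample size calculation section matches this: "We calculated that a sample of 676 participants was needed to detect an effect size of 0.3 with 90% power at a 5% significance level", with 338 per arm.

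The section on the impact of the COVID-19 pandemic revises the total to 672, split 360 intervention to 312 control, and adds: "Recalculation of the sample therefore results in an unequal allocation ratio with the optimal allocation ratio of 1.154 to 1 being employed". One reason given is that the internal pilot did not show the differential drop-out that had been anticipated, so the inflation of the control arm was removed. The changes belong to protocol version 4, dated 16 February 2021. Recruitment had resumed in November 2020.

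The section on progression to full trial reports: "The total number of randomisations across the five internal pilot sites for the first 6 months of recruitment was 123". It says that criteria were applied to decide whether pilot data could be used in the main trial, but does not state the result of that step.

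Under Statistical and economic analysis, the main mixed models are "adjusted for baseline score, allocation group, and stratification variables", with site as a random effect. The stratification variables are site, parent gender and self-referral status. Neither calendar period nor allocation-ratio period is listed.

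**The concern.** When the probability of receiving the intervention differs between two stretches of recruitment, randomisation makes the arms comparable within each stretch but not across the pooled sample. Later recruits are over-represented in the intervention arm and early recruits in the control arm. If outcomes drift over calendar time, part of the drift appears as a treatment effect.

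Drift is plausible here. Between the pilot and the later trial the article reports the pandemic pause, a move to remote data collection, variable group sizes and optional online support. Baseline adjustment removes a shift already visible at entry, but not a change in the course of well-being during follow-up. Site adjustment does not separate early from late participants within a site.

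The two statements of the ratio are also not linked. The Randomisation section gives 1:1 in the present tense. The COVID-19 section gives neither the date from which 1.154:1 applies nor whether it describes the whole sample or only new participants.

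**Working it through.** **Inputs.** From the article: 672 = 360 + 312; ratio 1.154; 123 randomised in the pilot; target difference 3 points, SD 10; ICC 0.05; attrition 20%; group size 6 to 13. Assumed: mean group size 9.5 (the midpoint); pilot data pooled; a period shift in WEMWBS of 3 to 5 points not captured by baseline or site. The number k randomised at 1:1 before the change is not given; 123 is a lower bound, and k = 200 is shown as an illustration.

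**1. The plan's own figures.** 360/312 = 1.1538, so the split and the ratio agree exactly. With clustering in the intervention arm only, the optimal ratio is the square root of the design effect. Analysed group size is 9.5 × 0.8 = 7.6, the design effect is 1 + 6.6 × 0.05 = 1.33, and √1.33 = 1.153. With 288 and 249.6 analysed, the standard error is 10 × √(1.33/288 + 1/249.6) = 0.93 points, and power is Φ(3/0.93 − 1.96) ≈ 0.90. The revised sample size is reproduced under these assumptions.

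**2. Arm totals on the two readings, k = 123.**
- 1.154:1 for new participants only: intervention = 61.5 + 549 × 1.154/2.154 = 355.6; control = 316.4; overall ratio 1.124.
- 1.154:1 as the overall target: the remaining 549 need (360 − 61.5)/(312 − 61.5) = 1.19 to 1.

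**3. Bias without a period term.** Bias = (early share of intervention arm − early share of control arm) × (early mean − late mean). Absolute sizes:

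| k at 1:1 | Final split | Early share, intervention | Early share, control | Difference | Bias, 3-point shift | Bias, 5-point shift |
|---|---|---|---|---|---|---|
| 123 | 355.6:316.4 | 17.3% | 19.4% | 2.1% | 0.06 | 0.11 |
| 123 | 360:312 | 17.1% | 19.7% | 2.6% | 0.08 | 0.13 |
| 200 (assumed) | 352.9:319.1 | 28.3% | 31.3% | 3.0% | 0.09 | 0.15 |
| 200 (assumed) | 360:312 | 27.8% | 32.1% | 4.3% | 0.13 | 0.21 |

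Against the standard error of 0.93, the range at k = 123 is 0.06/0.93 = 0.07 to 0.13/0.93 = 0.14 standard errors. The largest entry is 0.21/0.93 = 0.23.

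**4. Power.** At a group size of 9.5 without the attrition reduction, power is 0.8869 for 360:312 and 0.8867 for 355.6:316.4. The choice of reading has no practical effect on power.

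**The case against.** The strongest reply is that this is small and belongs elsewhere. The article condenses a fuller protocol, and its Data Availability section refers to a statistical analysis plan that is not at hand and may contain a period term. The COVID-19 section openly reports adaptations to the original design, so a careful reader can see that 1:1 has been superseded. Baseline WEMWBS is taken just before randomisation and should absorb much of any calendar shift. All of this lowers the stakes. It does not remove the point, because the article names the main-model covariates while also reporting the ratio change, and period is not among them.

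A second reply is that the ratio change may not line up with the pandemic changes, since recruitment resumed in November 2020 and version 4 is dated February 2021. That is fair: the article does not show that they coincide. The argument does not need it. Bias arises from any outcome difference between the two ratio periods, and a term defined by the ratio change addresses that directly.

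A reader might also infer that 360:312 is a mistake, because 1.154:1 applied after a 1:1 phase would give about 356:316. The documents do not support this. They never say that the ratio applies only to later participants, and 360:312 is exactly 1.154:1 over the whole sample. Even on the later-only reading the gap is about 4 per arm. This is not a sample-size error.

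**Conclusion.** The point holds as a modest analysis improvement together with a clarification. Allocation moved from 1:1 to 1.154:1 after at least 123 participants had been randomised, and the stated main model does not condition on the period that determined the allocation probability. If pilot and later data are pooled, an uncaptured shift of 3 to 5 WEMWBS points would bias the estimate by about 0.06 to 0.13 points with 123 early participants, and by up to about 0.2 with 200. The direction depends on whether well-being rises or falls over time. Bias of this size is unlikely to change the trial's conclusion.

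The result rests on assumptions about the size of the shift, the number who entered at 1:1 and the pooling of pilot data, none of which the article settles.

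**What to change.** - Add randomisation period (before or after the ratio change) as a fixed covariate in the main outcome models. If the ratio took more than two values, use one level per value. Specify this before outcomes are examined by arm.
- In the Randomisation and COVID-19 sections, give the date from which 1.154:1 applied and the number randomised at 1:1 by then. State whether it is the overall target (consistent with 360:312, and needing about 1.19:1 for the remaining 549 if 123 entered at 1:1) or the ratio for new participants (about 356:316 in total).

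The cost is one covariate derived from the randomisation date, one degree of freedom and two clarifying sentences. The arm numbers need no correction on this account.
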